# 4 PLAN FOR THE STUDY

## 4.1. Assessment criteria

**Myositides**

#### Primary criterion:

The evolution in muscle strength at 12 months, assessed by scores on the Kendall scale for different muscle groups (18) (see Appendix 1), is the primary criterion: for a given subject, this is the difference between the scores in each muscle group on the Kendall scale at M12 and the scores at D0.

#### Secondary criteria:

- - muscle strength defined on the Kendall scale (see Appendix 1) at D21, M6.5 (+/- 8 days) and M18
  - quality of life (SF 36 self-evaluation) (see Appendix 3)
  - CPK levels
  - autoantibody levels
  - extra-muscular activity for the disease, such as lung damage on pulmonary function tests.
  - doses or quantities of related immunomodulatory treatments.

Tolerance assessment criteria:

- - recording intercurrent events
  - blood pressure and heart rate readings
  - blood count, liver enzymes, etc. for the biological monitoring of the treatment

**Generalised myasthenia**

#### Primary criterion:

Evolution n muscle strength at 12 months using the MMG score (47, 48) (see Appendix 2), is the primary criterion: for a given subject, this is the difference between the subject's MMG score at M12 and his/her score at D0.

#### Secondary criteria:

- muscle strength defined by MMG score (47, 48) on day 21, at month 6 and at M18.

- MGFA postintervention status (45).

- ADLs score

- - quality of life (SF 36 self-evaluation) (see Appendix 3)

- number of clinical exacerbations that require either hospitalisation or a change in corticosteroid doses.

- corticosteroid doses and related treatments

- autoantibody levels

- vital capacity

Tolerance assessment criteria:

- - recording intercurrent events
  - blood pressure and heart rate readings
  - blood count, liver enzymes, etc. for the biological monitoring of the treatment

## 4.2. Description of the methodology

This is an open, perspective, multi-centre, phase II pilot study.

A total of 36 patients will be included, broken down as follows: 24 patients presenting myositis (12 suffering from myositis with anti-synthetase and 12 suffering from myositis with anti-SRP), and 12 patients suffering from generalised myasthenia.

## 4.3. Length of participation and description of the chronology of patient monitoring

## The expected inclusion period will be 2 3 years. The patients will participate for a period of 18 months and the total study period will be 4 5 years. Patients may not participate in any other biomedical study during the 18 months of their participation in this study.

### Pre-inclusion visit (W-4 to W-1) –Outpatient hospitalisation

Diagnosis procedure: patients with potential inflammatory myopathy associated with specific autoantibodies our generalised myasthenia will have been informed about the study in advance. After signed the informed consent, the patients will be pre-included and will be subject to the follow diagnosis procedure in order to confirm or reverse their inclusion:

**Myositides**

1. Clinical exam with testing according to the Kendall scale (18)
2. Echocardiography
3. EMG
4. MRI of the muscles
5. Chest scan and pulmonary function tests.
6. Full body scan and, depending on the clinical context, additional endoscopic exams.
7. Usual biological exams (CBC, serum electrolytes, full hepatic assessment, CRP, CPK) and immunoglobulin quantitation (IgG and IgM).
8. Blood tests for HIV, HBV, HCV, HTLV1
9. Muscle biopsy, if not done previously
10. Biological exams specific to the ancillary studies

**Generalised myasthenia**

1. Clinical exam with MMG and MGFA testing (44, 45)
2. Echocardiography
3. EMG
4. Pulmonary function tests
5. Chest scan (screening for a thymoma)
6. Usual biological exams (CBC, serum electrolytes, full hepatic assessment, CRP, CPK) and immunoglobulin quantitation (IgG and IgM).
7. Blood tests for HIV, HBV, HCV, HTLV1
8. Biological exams specific to the ancillary studies

### Inclusion period: Day – 1(D-1) to day + 2 (D2).

### Myositides and myasthenias

**Day – 1 (D-1)**:

Clinical exam with muscle testing and standard biological exams (CBC, serum electrolytes, full hepatic assessment (gamma GT, alkaline phosphatase, ASAT/ALAT, Bilirubin), CPK, ßhCG for women) specific to ancillary studies, quality of life, vital capacity for myasthenia.

**Day 0 (DO) to Day 2 (D2)**:

Infusion of the first rituximab dose (1000 mg) after related preventive measures have been completed, see details in Appendix 2.

After the first injection of rituximab: clinical exams including blood pressure, respiratory rate, oxygen saturation (finger), temperature every 15 minutes for the first 2 hours, after the infusion has started, then every 2 hours for the next 8 hours and finally 3 times a day until D2. (See the nurse's sheet).

Recording of intercurrent events and related medications

### Monitoring period: Days 7, 14, 21 and month 6.5 (+/- 8 days), 12 and 18:

**D7:**

Clinical exam and standard biological exams (CBC, serum electrolytes, full hepatic assessment, CPK)

Recording of intercurrent events and related medications.

**D14:**

Clinical exam and standard biological exams (CBC, serum electrolytes, full hepatic assessment, CPK) prior to infusion.

Infusion of the second rituximab dose (1000 mg) after related preventive measures have been completed.

After the injection of rituximab: clinical exams including blood pressure, respiratory rate, oxygen saturation (finger), temperature every 15 minutes for the first 2 hours, after the infusion has started, then every 2 hours for the next 8 hours (see the nurse's sheet).

Recording of intercurrent events and related medications

**D21**:

Clinical exam with neuro-muscular testing and standard biological exams (CBC, serum electrolytes, full hepatic assessment, CPK) specific to ancillary studies.

Recording of intercurrent events and related medications

**M 6.5 (+/-8 days)**:

Clinical exam with neuro-muscular testing (before the infusion), ßhCG levels, standard biological exams (CBC, serum electrolytes, full hepatic assessment, CPK) specific to ancillary studies.

Infusion of a maintenance dose of rituximab (1000 mg)

After the injection of rituximab: clinical exams including blood pressure, respiratory rate, oxygen saturation (finger), temperature every 15 minutes for the first 2 hours, after the infusion has started, then every 2 hours for the next 8 hours finally 3 times a day for 48 hours (see the nurse's sheet).

Recording of intercurrent events and related medications

**M12 (+/-8 days)**:

Clinical exam with neuro-muscular testing and standard biological exams (CBC, serum electrolytes, full hepatic assessment, CPK) specific to ancillary studies.

Neuromuscular assessment: EMG and muscle MRI (Myositis only)

Pulmonary function tests

Quality of life

Recording of intercurrent events and related medications

**M18 (+/-8 days): end of monitoring**

Final clinical exam with neuro-muscular testing and standard biological exams (CBC, serum electrolytes, full hepatic assessment, CPK) specific to ancillary studies.

Recording of intercurrent events and related medications

### Study design:

|  | W-4 to W-1 | D-1 | D0 | D1 | D7 | D14 | D21 | M6 | M12 | M18 |
| --- | --- | --- | --- | --- | --- | --- | --- | --- | --- | --- |
| Diagnostic procedure (with or without muscle biopsy) |  |  |  |  |  |  |  |  |  |  |
| Signature of the consent form |  |  |  |  |  |  |  |  |  |  |
| Rituximab (1000 mg) |  |  |  |  |  |  |  |  |  |  |
| Clinical exam |  |  |  |  |  |  |  |  |  |  |
| Neuro-muscular testing |  |  |  |  |  |  |  |  |  |  |
| Quality of life (SF 36) |  |  |  |  |  |  |  |  |  |  |
| VC (myasthenia) |  |  |  |  |  |  |  |  |  |  |
| Standard biological tests (CPK, etc.) |  |  |  |  |  |  |  |  |  |  |
| ßhCG (for women) |  |  |  |  |  |  |  |  |  |  |
| Intercurrent evts |  |  |  |  |  |  |  |  |  |  |
| Ancillary studies |  |  |  |  |  |  |  |  |  |  |

## 4.4. Rules for definitively or temporarily stopping the study

***Withdrawal from the trial***

A patient may leave the study at his or her own will (withdrawal of the patient's consent).

Whenever possible, a biological and clinical assessment at the time of the patient's withdrawal (within the month following the withdrawal of consent) will be carried out. Any subjects who leave the trial will not be replaced.

In all cases, the reason for leaving the trial will be noted in the case report form.

***Discontinuing treatment***

Treatment will be discontinued for the following reasons:

- tolerance problem, e.g. if continuing treatment is s threat to

the patient’s safety

- unpleasant side effects

- pregnancy before the 1st injection or during the study or any other reason that makes it impossible to continue

In all cases, the reason for discontinuing treatment will be noted in the case report form.

In addition, even if the patient no longer receives the treatment, he or she will not be considered as having left the trial. The patient will be assessed after the 18 months.

For a patient who is ***lost-to-follow-up***, every effort will be made to obtain updates about the patient (through the general practitioner or the family if necessary), and if possible to schedule a consultation.

# 5 Selection and exclusion of study subjects

## Myositides

## Inclusion criteria:

### - men and women aged between 18 and 70

- for women of reproductive age, use of effective contraception is required for the entire duration of their participation in the trial and for one year after the last rituximab infusion.

### - idiopathic inflammatory myopathies defined by:

1 – Myositis as defined by the 119th ENMC (18):

a) Proximal myopathy with muscle weakness.

Points a, b and c must be present.

b) Subacute onset or more slowly progressive in patients older than 18.

c) Muscle necrosis and regeneration and/or presence of inflammatory infiltrates in the muscle biopsy.

d) Myogenic syndrome on the EMG (optional criteria)

2 – Presence of specific autoantibodies: anti-synthetase (anti-JO-1, anti-PL-7 or anti-PL-12) or anti-SRP.

### - Resistant to conventional treatments

Resistance to conventional treatments is defined by an inadequate response or intolerable side effects with conventional treatments.

These treatments primarily include corticosteroids which must have been used continuously for longer than 6 months. But also, other immunosuppressants for which the prescription must not have been modified (except for adjustments to the doses) within the 3 months preceding inclusion. These are azathioprine, methotrexate, mycophenolate mofetil, cyclophosphamide, cyclosporine, polyvalent immunoglobulins and/or plasma exchanges. Thus, corticosteroids and at least two of these drugs or these therapeutic approaches (used sequentially or in combination) must have been tested successfully before inclusion, in accordance with the time frames indicated above. An inadequate response is defined as the absence of an improvement and/or a deterioration in the assessed parameters (muscle strength, vital capacity, increase in CPKs, etc.), in spite of these conventional treatments, causing the prescriber to modify or to reintroduce other treatments.

## Non-inclusion criteria:

1. Other muscle pathologies such as:
   1. Inclusion-body myositis.
   2. Macrophagic myofasciitis.
   3. Hereditary myopathies.
2. Inflammatory myopathies which are secondary to other connective tissue disorders:
   1. Systemic scleroderma (according to ARA criteria and/or LEROY and MEDSGER criteria).
   2. Sjögren's syndrome (European criteria).
   3. Systemic lupus erythematosus (ACR criteria).
   4. Rheumatoid arthritis (ACR criteria).
   5. Mixed connective tissue disease.
3. Cancers or myositides associated with cancer (22)
4. Under 18 years old or over 70 years old
5. Failure to sign the informed consent form
6. Patient not affiliated with the social security regime
7. History of severe allergic reaction or anaphylactic reaction to a murine monoclonal or humanised antibody, or known hypersensitivity to one of the components of rituximab.
8. History of severe allergic reaction or anaphylactic reaction to methylprednisolone.
9. Severe heart or pulmonary condition (in the opinion of the investigator: to be documented in the CRF).
10. Presence of an uncontrolled concomitant disease, such as a condition affecting the central nervous system, kidneys, or liver, or an endocrine or gastro-intestinal condition, which in the investigator's opinion does not allow the patient to be included.
11. Active infection of any kind. History of recurrent or chronic severe infection. History of deep infection related to fasciitis, abscess, osteomyelitis during the previous 52 weeks.
12. Immunodeficiency syndrome, including seropositivity for HIV.
13. Surgical operation scheduled in the year following inclusion.
14. Any type of vaccination during the previous 28 days (it is advisable to seriously consider the indication of a vaccination (e.g. a flu vaccine for a patient suffering from a neuromuscular condition) prior to treatment with rituximab and to carefully assess the efficacy (which may be completely lost simply due to the action mechanism of rituximab). In other words, the need to vaccinate patients must be anticipated well in advance of 28 days prior to the rituximab injection. The use of a live attenuated vaccine is prohibited for the entire duration of the study (and for the 28 days prior to the study).
15. Treatment with any experimental agent within 28 days of the infusion or at 5 half-lives of the drug in question (the longest of these two time frames is to be taken into account).
16. Previous treatment (within one month of inclusion) with a cell depletion therapy, of any kind whatsoever, such as, for example, CAMPATH, anti CD4, anti CD5, anti CD3, anti CD19, anti CD11a, anti CD22, anti-Blys/BA.
17. Positive serum ßhCG result at the screening or any other positive pregnancy test carried out before the first rituximab injection.
18. Pregnancy or breast feeding or attempting to become pregnant during the study.

19. Positive **hepatitis B** test (positive Hbs antigen and/or positive PCR HBV).

However, patients presenting previous hepatitis that has been cured (AgHBS negative, Ac anti-Hbc +/-, Ac anti-Hbs+) can be included with specific monitoring for Ag  Hbs and PCR HBV every three months and 6 months after the end of the Study or **hepatitis C**.

20. Haemoglobin < 8.0 g/dL

21. Polynuclear neutrophil <1.5 X 10 ³/µL.

22. IgG and/or IgM levels < 5.0 and 0.40 mg /mL, respectively.

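### The hepatitis B criteria state no rule for an isolated anti-HBc patient: read literally, such a patient may be enrolled with no required HBV-specific test after screening

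*Protocol*

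**What the plan says.** The two disease groups share the same hepatitis B wording (Protocol section 5, Non-inclusion criteria: 19 for myositis, 17 for generalised myasthenia).

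- Exclusion applies to a positive hepatitis B "test (positive Hbs antigen and/or positive PCR HBV").
- An exception sentence follows: "patients presenting previous hepatitis that has been cured (AgHBS negative, Ac anti-Hbc +/-, Ac anti-Hbs+) can be included with specific monitoring for" HBs antigen and HBV PCR. The schedule reads "PCR HBV every three months and 6 months after the end of the Study".

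Outside these criteria, HBV testing appears only at the pre-inclusion visit (section 4.3), as "Blood tests for HIV, HBV, HCV, HTLV1". From D-1 on, the visits call for a liver panel, spelled out at D-1 as "full hepatic assessment (gamma GT, alkaline phosphatase, ASAT/ALAT, Bilirubin"). The D21 entry, for example, lists "standard biological exams (CBC, serum electrolytes, full hepatic assessment, CPK) specific to ancillary studies". The pre-infusion panel under Assessment of Rituximab's toxicity also covers liver enzymes and bilirubin. None of these lists names an HBV marker.

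**The concern.** The protocol judges that past hepatitis B needs HBsAg and PCR testing during rituximab, and it includes anti-HBc among the markers that describe such a patient. Yet the required marker in the monitored profile is anti-HBs. A patient with anti-HBc alone, and no antigen or detectable DNA, falls between the exclusion and the monitoring rule.

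What is at stake is safety. Section 6.2 names viral reactivation as a documented risk of rituximab. Section 6.3 recommends that an immunosuppressant be maintained alongside it. The rules for stopping rituximab require permanent discontinuation after a serious viral reactivation, which presupposes that the reactivation is detected.

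**Working it through.** No statistical figure in the protocol is involved. The check runs the serological patterns through the rules and then counts the scheduled tests.

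**Step 1: patterns.** HBsAg-positive or PCR-positive patients are excluded. For the rest, two antibodies with two results each give 2 × 2 = 4 patterns:

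| Anti-HBc | Anti-HBs | What criteria 19 and 17 say |
|---|---|---|
| + | + | Cured profile: included with HBV monitoring |
| − | + | Cured profile if there was previous hepatitis: included with HBV monitoring |
| − | − | No marker; not excluded and no monitoring called for |
| + | − | Not excluded; outside the monitored profile; no rule |

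**Step 2: do other criteria catch the fourth row?** Myositis criterion 10 (item 8 for myasthenia) requires "Presence of an uncontrolled concomitant disease, such as a condition affecting the central nervous system, kidneys, or liver", judged by the investigator to prevent inclusion. Serology alone does not meet that. Criterion 11 (item 9) reads "Active infection of any kind. History of recurrent or chronic severe infection". A patient with no antigen and no detectable DNA does not clearly meet that either.

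**Step 3: HBV-specific tests after screening.**

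- Fourth-row patient: 0 required.
- Monitored patient, if the schedule means three-monthly tests in the 18 months plus one test 6 months later: M3, M6, M9, M12, M15, M18 = 6, and 6 + 1 = 7.
- Monitored patient, if it means three-monthly tests continuing for 6 months after the study: 6 + 2 (M21, M24) = 8.

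**Step 4: liver panels.** Section 4.3 gives D-1, D7, D14, D21, M6.5, M12 and M18 = 7 panels, 3 of them after D21. The synopsis also lists a biological analysis at D0 without giving its content; this does not alter the later spacing.

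Taking M6.5 as day 198, M12 as day 365 and M18 as day 548:

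- D21 to M6.5: 198 − 21 = 177 days = 25.3 weeks
- M6.5 to M12: 365 − 198 = 167 days = 23.9 weeks
- M12 to M18: 548 − 365 = 183 days = 26.1 weeks

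M6.5, M12 and M18 each have a window of 8 days either way; D21 has none stated. The three gaps can then run 169–185, 151–183 and 167–199 days, so about 22 to 28 weeks overall.

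**Step 5: after the third infusion.** From M6.5 to M18 is 548 − 198 = 350 days (334 to 366 with the windows). In that span the fourth-row patient has 2 later liver panels (M12, M18) and 0 required HBV tests. A monitored patient has 4 HBV tests (M9, M12, M15, M18) under either reading of the schedule.

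**The case against.** The strongest reply is that the literal reading is not the only one. If only antigen-positive or PCR-positive patients were barred, a cured patient would already be eligible, and the exception sentence would add nothing but the monitoring. The permission has its full effect only if past hepatitis B outside the cured profile is not admitted, and then the isolated anti-HBc patient is excluded. The sentence is also poorly drafted, ending in a stray reference to hepatitis C, so little should rest on its punctuation. This stands to the extent that the intent is uncertain. It does not remove the point: the exclusion defines itself by antigen and PCR alone, and the stricter rule is nowhere written.

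The alternative that the plus/minus sign means with or without anti-HBs is weaker, because anti-HBs is listed separately with its own plus sign.

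A reader might infer that these patients have no safety oversight. The documents do not support that. Liver panels continue throughout. Section 3.3 has the independent committee meet after the first 4 inclusions and decide whether to proceed. Section 8.1.2 adds meetings after the first 4 patients on azathioprine and the first 4 on mycophenolate mofetil, and lets the committee interrupt the study at any time. Section 8.1.1 has the steering committee follow tolerance. Investigators may also test at their discretion. These safeguards are real, but none of them requires an HBV test.

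A reader might also take section 6.2 as naming hepatitis B reactivation. It does not; its examples are EBV, VZV and JC virus.

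Finally, the terse HBV entry in the screening list is mostly a matter of detail, since applying the criteria already implies the four assays.

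**Conclusion.** The point holds as a gap in the wording of criteria 19 and 17. Read literally, one of the four antibody patterns among HBsAg-negative, PCR-negative patients carries an HBV marker but has no rule. It leads to 0 required HBV-specific tests after screening, against 7 or 8 for a monitored patient, with liver panels about 24 to 26 weeks apart after D21.

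One in four patterns is not one in four patients. The protocol gives no basis for the number affected; with 36 patients it is probably very small and may be zero. The texts do not show that the sponsor meant to enrol such patients unmonitored, only that nothing written prevents it.

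The conclusion rests on the literal reading and on one assumption from general serology that the protocol does not state: anti-HBc without anti-HBs can mark past HBV infection. The efficacy endpoints, the target of 12 per group and the 6-responder rule are unaffected.

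**What to change.** Reword the exception sentence in both criteria: any HBsAg-negative, PCR-negative patient who is anti-HBc-positive, whatever the anti-HBs result, is included only with the HBsAg and HBV PCR monitoring the protocol already prescribes (every three months, and 6 months after the end of the study).

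The sponsor should first confirm its intent, because this wording would loosen eligibility if the pattern was meant to be barred. In that case, state the exclusion of isolated anti-HBc explicitly instead.

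The cost is one sentence in two places. With monitoring, it adds 7 or 8 HBsAg/PCR samples for each such patient. With exclusion, a rare candidate is lost at screening, before inclusion, so the group targets stand and only recruitment may slow. Naming the HBV assays in the two screening lists would be a convenience and is not essential.

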**Generalised myasthenia**

## Inclusion criteria:

### - men and women aged between 18 and 70

- for women of reproductive age, use of effective contraception is required for the entire duration of their participation in the trial and for one year after the last rituximab infusion.

### - Generalised myasthenia defined by:

Seropositive generalised myasthenia as defined by the TEXAS CLINICAL CLASSIFICATION SYSTEM (43), at a clinical stage > class III (IVa, IVb or V), i.e., with sever weakness affecting the limbs or the axial muscles (class IVa), or bulbar and respiratory damage (class IVb), or requiring mechanical ventilation (class V).

1. Severe weakness (class IVa, IVb or V) in the extra-ocular muscles quantified in the myasthenic score (MMS) and for which inter-and intra-observer reproducibility has been shown (44).
2. Presence of specific autoantibodies: anti-RAch.

### - Resistant to conventional treatments:

Resistance to conventional treatments is defined by an inadequate response or intolerable side effects with conventional treatments.

These treatments primarily include corticosteroids which must have been used continuously for more than one year. But also, other immunosuppressants for which the prescription must not have been modified (except for adjustments to the doses) within the 6 months preceding inclusion. These are azathioprine, mycophenolate mofetil, methotrexate, cyclophosphamide, cyclosporine, polyvalent immunoglobulins and/or plasma exchanges. Thus, corticosteroids and at least two of these drugs or these therapeutic approaches (used in combination) must have been tested successfully before inclusion, in accordance with the time frames indicated above. An inadequate response is defined as the absence of an improvement and/or a deterioration in the assessed parameters (muscle strength, vital capacity, etc.), in spite of these conventional treatments, causing the prescriber to modify or to reintroduce other treatments.

